# Educational strategy for the development of skills in exchange transfusion: a randomized clinical trial protocol

**DOI:** 10.1186/s13063-020-04312-3

**Published:** 2020-05-07

**Keywords:** Newborn, Simulation training, Virtual, Telemedicine, Objective Structured Clinical Examination (OSCE), Individual assessment, Safety training, Simulation centre

## Abstract

**Background:**

Exchange transfusion is a highly complex procedure that requires high levels of expertise. Trainee paediatricians do not have adequate training in exchange transfusion because opportunities to perform this procedure in practice are scarce. This protocol seeks to compare two educational interventions for exchange transfusion that allow students to develop competencies to perform the technique in an appropriate and safe way.

**Methods/design:**

This is a randomized parallel single-blind clinical trial with allocation by simple randomization to the educational intervention (simulation or a digital didactic environment). Students from the paediatric specialization who volunteer to participate will be included. A practical evaluation of the procedure will be performed through a simulated scenario using a standardized clinical case. The main outcome is defined as the result of evaluation using the Objective Structured Clinical Examination; superior performance will be defined when the percentage is greater than or equal to 85%, and non-superior performance will be defined when the result is less than 84%. The chi-square independence test or the Fisher exact test will be used to evaluate the effect of the interventions. Multivariate analysis will be performed using a non-conditional logistic regression model. Stata 15® software will be used.

**Discussion:**

Exchange transfusion is a procedure that requires expertise to achieve adequate outcomes. The inclusion of new educational strategies, such as simulation and digital didactic environments, is seen as a training option that can improve performance in clinical skills, reduce adverse events and increase the level of trust.

**Trial registration:**

ClinicalTrials.gov: NCT04070066. Registered on 28 August 2019. https://clinicaltrials.gov.

## Background

### Scientific background and justification

Exchange transfusion is a highly complex procedure, performed in neonatal intensive care units under specific medical indications, that requires a high level of expertise [1]. It should be performed only by trained personnel in a neonatal or paediatric intensive care unit equipped with complete monitoring and with the capacity to perform resuscitation if necessary [2]. The need for exchange transfusion has notably decreased with the prevention of haemolytic disease due to rhesus (Rh) incompatibility and with the systematic application of the clinical practice guidelines of the American Academy of Pediatrics (AAP), published in 2004, for the identification and treatment of new-born babies at risk of severe hyperbilirubinemia [3]. Because exchange transfusion is a rare procedure, paediatricians in training do not have experience with it. Opportunities in daily practice to develop skills in exchange transfusion are rare, and professionals in paediatrics do not reach a sufficient level of competence to master this procedure in the clinical setting [4].

Clinical simulation scenarios and digital teaching environments are postulated as valid and effective teaching options for the development of competencies in medical personnel in training at the postgraduate level [5]. The use of simulation-based training as an educational tool has become an increasingly accepted method for improving the skills of health personnel in a safe learning environment [6]. Simulation standardizes and guarantees exposure to a specific event, allows the teaching of specific clinical skills, decreases the generation of error, increases the safety of the patient and the student, and improves clinical judgement [7–10]. On the other hand, the use of digital environments facilitates learning through interactive tools and is postulated as an effective model for the acquisition of knowledge in medical schools.

We are not aware of reports on the use of simulated learning strategies compared to strategies based on digital didactic environments, particularly in the evaluation of competencies in exchange transfusion.

The implementation of educational strategies related to exchange transfusion during the training of future paediatricians could positively impact the health outcomes of patients who require this procedure [11]. This protocol, through a controlled clinical trial, seeks to compare two educational interventions in exchange transfusion, one based on simulation and another based on the development of a digital didactic environment, for the development of competencies in exchange transfusion performed by postgraduate students in paediatrics.

### State of the art

The use of simulation to teach the knowledge, skills and behaviours necessary for effective paediatric resuscitation has become widespread and has been massively adopted by paediatric institutions; it is of vital importance in topics such as neonatal resuscitation. Studies such as that of Sawyer [12] suggest that simulation education is associated with improved performance in neonatal resuscitation skills and propose the use of simulation in training. Gaies [13], using a randomized controlled trial, compared the standard teaching method with simulation-based modules for training in the performance of frequent paediatric procedures, such as bag mask ventilation, venipuncture, peripherally inserted central catheter and lumbar puncture; it was shown that the participants in the simulation group performed the peripheral insertion of the central catheter more successfully than the controls (78% vs. 35%; *P* = 0.01) and obtained significantly higher scores on the knowledge tests for various procedures and on checklists for the peripheral insertion of a central catheter (81% vs. 61%; *P* = 0.003) and lumbar puncture (77% vs. 68%; *P* = 0.04) in the initial evaluation [13]. Sudikoff studied and evaluated the effectiveness of a simulation session and teamwork in the management of the paediatric airway by paediatric residents in comparison with a group that did not receive the simulation intervention, and found that the intervention group had higher scores (*P* < 0.05), fewer adverse events and more positive teamwork [14].

On the other hand, in relation to teaching in digital didactic environments in paediatrics, Kessler et al. conducted a randomized controlled trial in paediatric residents and proposed that there is no difference in the effects of lumbar puncture audiovisual training combined with simulation versus audiovisual training alone. Despite better success rates in the first simulated attempt immediately after audiovisual training, with control 6–8 months later, no statistically significant differences were found between the groups in their comfort, knowledge base or performance on the Objective Structured Clinical Examination (OSCE) [15]. Tofil et al. conducted a prospective observational cohort study to evaluate the comfort and performance of second-year residents in simulated resuscitation scenarios and procedural skills, particularly intraosseous needle insertion and intubation, as a result of weekly 1-h sessions during paediatric intensive care rotations accompanied by video simulation assistance; their study showed that the intervention increased the residents’ general confidence in the management of various paediatric resuscitation events and their perceived capability [16].

## Methods

### Study design

This is a randomized, parallel, single-blind trial with 1:1 allocation to the interventions studied.

### Study subjects

Students in the paediatrics specialization, who meet the inclusion criteria and who wish to participate voluntarily and sign informed consent, will be included. In Colombia, there are currently 700 students in the paediatrics specialization, who are members of the Colombian Society of Pediatrics, and all of them are going to be invited by e-mail, to participate in the study. The inclusion criteria are as follows:
Men and women of legal age who are students enrolled in a paediatrics specialization programme at Colombian university medical schoolsStudents in any year of specialization in paediatrics

The exclusion criterion is participation in rotation outside Columbia as part of the curriculum.

### Interventions

#### Detailed description of the procedure

The study protocol was developed in the simulation laboratory (simulated hospital) of the Universidad de La Sabana (University of La Sabana), and in a virtual didactic environment. Planning and structuring will be carried out by neonatology and paediatric medical education teachers at the School of Medicine of the Universidad de La Sabana (University of La Sabana).

Once a student has agreed to participate and provided signed informed consent, he or she will be entered into the study protocol (Fig. 1). Initially, students all participating students will receive a theoretical guide on exchange transfusion to study and analyse on their own in advance of the intervention. This guide is the only document that will be provided, prior to randomization. The guide includes aspects such as indications for exchange transfusion, objectives, step-by-step technique, preparation of the newborn, necessary supplies for implementation and complications.

**Fig. 1 Fig1:**
[figure not shown]
Flow diagram of enrolment, intervention, and assessment. OSCE, Objective Structured Clinical Examination

**Fig. 2 Fig2:**
[figure not shown]
Schedule protocol. OSCE, Objective Structured Clinical Examination

Subsequently, the students will be assigned to an educational intervention (simulated scenario or digital didactic environment) by randomization in permuted blocks (see “Randomization and blinding”) (Fig. 2). Both educational techniques will have the following objective: the student will be able to identify, know and/or perform the indications of the procedure, the preparation and disposition of the supplies and materials necessary for the procedure, the preparation of the newborn for exchange transfusion and the step-by-step procedure. The two techniques will be implemented as follows:
Simulated scenario:- The educational intervention will be developed in the simulation laboratory. - The students will observe the exchange transfusion procedure and will be able to practice in the procedure under the supervision of a neonatology expert. - The neonatologist in charge of the training of the simulation group, knows from the beginning the assigned intervention group. - For the training, neonatal high-fidelity simulators, clinical history and paraclinical exams, necessary supplies for the procedure, a simulated mother, a professional nurse and a nursing assistant will be available. - Training will take place in individual skill stations (identification of indications, communication, management of medical devices and procedures) and in integrated clinical scenarios.Digital didactic environment:- Students assigned to this group will receive access to a digital didactic environment where they will have at their disposal the exchange transfusion guide and a complete video explaining the indications, the preparation of supplies and the newborn for the procedure, the management of medical devices required and a step-by-step description of the exchange transfusion technique. - The student will see an integrated clinical case. - This video will be developed by the neonatology and paediatric medical education teaching team in the simulation laboratory of the university using neonatal high-fidelity simulators, a simulated mother and the necessary medical equipment and supplies (the video can only be seen by each participant, a maximum of three times).

At 4 weeks, after the training is over, the students will be scheduled for a practical evaluation of the procedure in the simulation laboratory at the Universidad de La Sabana (University of La Sabana) (Fig. 2). For this evaluation, a simulated scenario will be developed using a standardized clinical case with a simulated patient according to the OSCE methodology. All participation sessions during the OSCE evaluation will be video and audio recorded to allow the reviewer/evaluator, who will be blinded to the educational intervention assigned to the student, to apply the checklists at a later time. In order to maintain the participant students, we will use study through materials and e-mails, during the time period of the study.

#### Outcome measures

The outcome measures are as follows:
Main outcome: overall result of the OSCE evaluation (checklist). The performance score will be the score obtained for the evaluation divided by the maximum possible score of the test and multiplied by 100. A superior performance is defined as a score greater than or equal to 85%, and a non-superior performance is defined as a score equal to or less than 84%.Secondary outcomes: performance on the OSCE checklist in the following sub-areas:Clinical history and approach to patient risk and indication for exchange transfusion.Comprehensive assessment of the patient with neonatal jaundice.Management of the patient with neonatal jaundice and indication for exchange transfusion.

The OSCE and the instrument (checklist) for evaluating students were developed using consensus methodology performed by a panel of neonatologists or paediatricians who are experts in the exchange transfusion procedure. Subsequently, in a second phase, the validity and reliability of the OSCE created by consensus will be tested.

The instrument consists of the following areas, within which the items to be evaluated are described:
Clinical history of and assessment of risk to the patient with neonatal jaundice: The student should obtain information about the risk factors to classify patients through an interview with the parents and the study of the clinical history.Comprehensive assessment of the patient with neonatal jaundice: the student should evaluate the patient’s need for exchange transfusion by performing a physical exam and requesting paraclinical tests and their interpretation. The student should indicate the treatment and communicate the decision to the parents.Management of the patient with neonatal jaundice and indication for exchange transfusion: the student must perform exchange transfusion in the newborn and, to do so, must prepare the necessary elements, determine the replacement fluid and volume, evaluate the patient’s condition, prepare and monitor the newborn and identify possible complications.

Each item will be classified on an ordinal scale: 2 points if the student fulfils the entire evaluated item correctly, 1 point if the student partially meets the evaluated item, and 0 if he or she does not. The total score obtained will be divided by the maximum possible score and multiplied by 100.

### Sample size

No previous studies were identified that compared simulation to a digital platform in the development of exchange transfusion competencies. A randomized trial that compared success rates in the performance of frequent paediatric procedures, such as bag mask ventilation, venipuncture, peripherally inserted central catheter and lumbar puncture, identified advantages with simulation compared to standard teaching. This study identifies absolute differences in the likelihood of success of 33%, 20% and 9% in favour of the simulation for the insertion of a central line, peripheral catheter and lumbar puncture, respectively [13]. A 30% difference in the probability of having an acceptable exchange transfusion procedure is considered acceptable when comparing the two teaching interventions [13]. Based on this difference, and for power of 80% and a type I error level of 5%, 80 participants are required (40 per group).

### Randomization and blinding

Students will be assigned to the study groups using a computer-generated randomization sequence. This process will be centralized in the paediatric office of the Universidad de La Sabana (University of La Sabana). The sequence will be generated through the Research Randomizer page (www.randomizer.org), and a permuted blocks strategy with a block size of 8 will be used. The permuted blocks strategy and the size of the blocks will not be known by the researcher. The random sequence be concealed by placing the allocation in opaque envelopes at the time of assignment.

The researcher and the student cannot be masked to the allocation due to the nature of the interventions. However, the research team responsible for data analysis will be blinded to the allocation as will the expert neonatologist who evaluates the video-recorded procedures using the checklist. The database will be coded and the identification code will not be available to the analyst.

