### Statistical analysis

The participants will be described using descriptive statistics. Quantitative variables will be presented as measures of central tendency and dispersion, and qualitative variables as absolute and relative frequencies.

Effect of the intervention: the outcome of the study will be a score equal to or greater than 85% on the OSCE; therefore, the outcome variable will be dichotomous. The chi-square independence test (or the Fisher exact test if the assumption of at least 5 counts per cell is violated) will be performed to evaluate the effect of the interventions. Additionally, relative risk and the respective 95% confidence interval will be estimated as a measure of effect.

Multivariate analysis will be performed using a non-conditional logistic regression model, with the outcome of the study as the dependent variable and the intervention and year of training as the independent variables. Interim analyses will not be performed. Two-tailed analyses will be performed for a type I error level of 5%. The Stata 15® programme will be used in the analyses.

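### Year of training is the only adjustment covariate, yet the main test and relative risk ignore it and the randomization is not stratified by it

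*Protocol article*

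**What the plan says.** Study subjects (Protocol article) admits residents at every stage of the specialization; the expected mix of years is not given. Study design describes a "single-blind trial with 1:1 allocation to the interventions studied". Randomization and blinding specifies the tool, the block size and the concealment, and states that "a permuted blocks strategy with a block size of 8 will be used". It names no stratification factor. The abstract instead speaks of "allocation by simple randomization to the educational intervention". The two descriptions should be reconciled, but neither balances year of training.

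In Statistical analysis the endpoint is binary: "the outcome of the study will be a score equal to or greater than 85% on the OSCE". The effect is evaluated without covariates: "The chi-square independence test (or the Fisher exact test if the assumption of at least 5 counts per cell is violated) will be performed", and "relative risk and the respective 95% confidence interval will be estimated as a measure of effect". Year of training enters only in the logistic model, "with the outcome of the study as the dependent variable and the intervention and year of training as the independent variables". The section does not rank the crude and adjusted analyses or say what happens if they disagree.

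**The concern.** The authors thought year of training worth adjusting for and chose no other covariate. The OSCE also scores history-taking, risk classification, examination, interpretation of tests and communication with parents. These are general skills that plausibly grow with seniority. If year affects the chance of reaching 85%, an arm that happens to receive more senior residents will look better for that reason, and neither the chi-square test nor the crude relative risk corrects for it.

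The adjusted model reports on another scale. At assumed success of 50% versus 80%, the relative risk is 0.80/0.50 = 1.60 and the odds ratio is (0.80/0.20)/(0.50/0.50) = 4.0. A reader given a crude relative risk and an adjusted odds ratio cannot easily tell whether they differ because of imbalance or because of scale. At stake is how clearly one trial of 80 can be interpreted, not whether its test is valid.

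**Working it through.** **Inputs from the article.** 80 participants, 40 per arm; 30-point difference; 80% power; two-sided 5%; blocks of 8, 1:1. **Assumed, because the article does not give them:** three equal year groups, the success rates by year, and the base success rate.

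**1. The stated sample size.** With pooled variance, n per arm = [1.96√(2p̄(1−p̄)) + 0.842√(p₁(1−p₁) + p₂(1−p₂))]² / 0.30². For 50% versus 80%, p̄ = 0.65 and n = (1.322 + 0.539)²/0.09 = 38.5, so 39. For 45% versus 75% it is 41. The unpooled formula at 35% versus 65% gives (1.96 + 0.842)² × 0.455/0.09 = 39.7, so 40. The stated 40 per arm is reproduced, and nothing below changes it.

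**2. How uneven can the arms be?** If 27 of 80 are final-year, the number x in one arm is hypergeometric, and the difference in share is (2x − 27)/40.
- Variance of x = 40 × (27/80) × (53/80) × (40/79) = 4.53, so the SD of the difference is 2 × 2.13/40 = 10.6 points.
- The difference is at least 10 points in 34% of trials, at least 15 points in 16% and at least 20 points in 6%.
- Simulation with blocks of 8 gives an SD of about 10.5 points with one list and 2.5 points with a list per year. With lists by year, 20-point differences virtually disappear.

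**3. What does that do to the crude estimate?** The shift in the crude risk difference has SD ≈ σ√(1/40 + 1/40) = 0.224σ, where σ is the SD of success across years.

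| Assumed success by year | σ | SD of shift | 95th percentile of size (simulated) |
|---|---|---|---|
| 40/50/60% | 8.2 points | 1.8 points | 3.5 points |
| 30/50/70% | 16.3 points | 3.6 points | 7.0 points |
| 20/50/80% | 24.5 points | 5.5 points | 10.5 points |

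The mean shift is zero in every row. For scale, take true rates of 50% and 80% (relative risk 1.60) and a 7.0-point shift split equally between the arms. The expected rates become 53.5% versus 76.5% (relative risk 1.43) or 46.5% versus 83.5% (1.80).

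**4. Type I error of the crude test, one list.** Simulated rejection under the null with mean success of 50% is 5.4% to 5.8%. It is 5.7% when year has no effect at all, so the small excess over 5% does not come from seniority. Only within the 10% of trials with the largest imbalance does it rise: to 6.2%, 11.7% and 15.4% for the three rows above. A year-adjusted Mantel-Haenszel test, used as a stand-in for the planned logistic model, stays at 4.9% to 5.0% in the same three rows without stratified lists.

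**5. Power for a 30-point effect** (digital-arm success 30/50/70% by year).

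| | Crude chi-square | Year-adjusted test |
|---|---|---|
| One list | 81.9% | 86.6% |
| List per year | 84.0% | 87.2% |

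If year has no effect, adjustment gains nothing. At 50% versus 80% with one list, power goes from 81.5% to 80.8%. At less favourable base rates the loss with one list is about 2 to 3 points; with lists by year it is about 0 to 1 point.

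**The case against.** The strongest case on the other side is that nothing here is an error. Unstratified permuted blocks are a standard, valid design. The article already plans a model that adjusts for year, and that model keeps its error rate without stratification. Once year is adjusted for, stratifying adds only 87.2 − 86.6 = 0.6 points of power. All of this stands, and it is why the remedy puts the analysis first and the lists second.

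It is also fair that the article never calls year of training prognostic; that is inferred from its being the sole covariate. The Background and Discussion say residents get little exposure to the procedure, and every participant receives the same theoretical guide first. Both could make the year effect small, and the rates by year used above have no support in the article.

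A reader might go further and infer that the randomization is defective, or that seniority will bias the main comparison. The documents do not support that: the mean shift is zero, the overall error rate is near nominal, and large imbalances are the tail, not the expectation. Nor does the article label the chi-square test primary or the regression secondary. The ranking is read from its statement that the chi-square or Fisher test evaluates the effect.

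A full analysis plan could settle the order of precedence. It could not stratify an allocation already made.

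**Conclusion.** The point holds as a modest, inexpensive improvement in balance and precision, not as a correction of an invalid design. The crude test and relative risk carry the main conclusion without the one covariate the plan models. With 80 participants, a difference of 20 points or more in final-year share would occur in about 6% of trials. The crude risk difference would typically shift by 2 to 5 points (SD) against a target of 30. In the 30/50/70% scenario, adjusting for year raises power by about 5 points; if year has little effect it gains nothing and may cost up to 2 to 3 points without lists by year. These sizes depend on the assumed three equal year groups and success rates by year. The structural facts (no stratification, unadjusted main analysis, no stated precedence) are the article's own.

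**What to change.** Make a year-adjusted effect the main estimate and test, with year of training as a categorical factor: for example, a Mantel-Haenszel or model-standardised relative risk with its 95% confidence interval. Report the crude chi-square (or Fisher) test and crude relative risk as supportive, and say in advance that the adjusted result prevails. Year is already in the planned model, so this needs no new data and no change to the sample size.

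Trial status says recruitment has not begun, so also generate a separate permuted-block list and envelope set for each year of training. The cost is a few more lists and incomplete blocks that leave the arms unequal by one or two students (about 1.5 on average in simulation). If year has little effect, the adjusted test brings no gain: it may lose about 2 to 3 points of power with a single list, and about 0 to 1 point with lists by year. That is a further reason to make both changes together.

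### The abstract and Methods disagree on the allocation method, and printing the fixed block size of 8 undercuts the promise that the researcher will not know it

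*Protocol article*

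**What the plan says.** The protocol article describes the allocation method in three places.

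- Abstract, Methods/design: "allocation by simple randomization to the educational intervention".
- Interventions (text with Fig. 2): students are assigned "by randomization in permuted blocks".
- Randomization and blinding: "a permuted blocks strategy with a block size of 8 will be used".

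The Randomization and blinding section then adds a safeguard: "The permuted blocks strategy and the size of the blocks will not be known by the researcher". The same section says of central handling: "This process will be centralized in the paediatric office of the Universidad de La Sabana". On concealment it says: "The random sequence be concealed by placing the allocation in opaque envelopes at the time of assignment". On masking it says: "The researcher and the student cannot be masked to the allocation due to the nature of the interventions". The evaluator of the recordings and the data analysts are blinded.

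The article was published on 7 May 2020. Trial status says that recruitment had not started and gives November 2020 as its beginning.

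**The concern.** There are two separate defects. First, simple randomization and permuted blocks are different methods, and the current text asserts both. Someone who reads only the abstract would report the wrong design.

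Second, the protocol relies on the researcher not knowing the blocking or the block size, and then publishes both. Knowledge of a fixed block size becomes useful when earlier assignments are visible, and the researcher is unmasked. If the person enrolling can foresee the next arm, the order in which volunteers are enrolled or scheduled can come to depend on it. Blinded scoring of the recordings protects the outcome assessment but not the make-up of the groups. Students in any year of training are eligible, and the protocol treats year as relevant by putting it in the logistic model, so the groups could plausibly differ in ways that matter.

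**Working it through.** **Inputs.** Block size 8 (Randomization and blinding), 1:1 ratio (Study design), 80 participants with 40 per group, a 30-point difference, 80% power and 5% type I error (Sample size), two-tailed (Statistical analysis). The protocol gives no control rate, so any rate used below is an assumption.

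**The plan's own figure.** Take 78% for simulation, the central-catheter rate of the cited trial (State of the art), and subtract 30 points to get 48%. With pooled variance, n per group = [1.96·√(2·0.63·0.37) + 0.8416·√(0.78·0.22 + 0.48·0.52)]² / 0.30² = (1.338 + 0.546)² / 0.09 ≈ 39.5, rounded up to 40. The total is 80, as stated. Nothing below changes it.

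**Assignments known with certainty in a 4:4 block.** An assignment is certain in advance only if all four places of the other arm are already used. For any one place this has probability 1/(4+1) = 1/5. Over the block, 8 × 1/5 = 1.6 of 8, or 20%. The 80 participants make 80/8 = 10 blocks, so the expected number is 16.

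**Correct guesses.** The best strategy is to guess the arm with more places left and to toss a coin at ties. For m per arm, the expected number correct is m + 2^(2m−1)/C(2m, m) − 1/2. With m = 4 this is 4 + 128/70 − 0.5 = 5.33 of 8, or 66.6%. Exact recursion over the block gives the same value. Simple randomization gives 50%.

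Both results assume an observer who knows the block size and has followed every earlier assignment in order.

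**How far the two stated methods differ.** Under simple randomization of 80, the size of one arm is Binomial(80, 0.5).

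| Split | Probability |
|---|---|
| exactly 40:40 | 8.9% |
| arms differ by 8 or more | 43% |
| 35:45 or worse | 31.4% |

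Ten complete blocks of 8 give 40:40 by design.

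**Effect on power.** Going from 40:40 to 35:45 lowers power from 77.6% to 77.0% (assumed rates 35% and 65%) or from 81.6% to 80.6% (assumed rates 50% and 80%). The loss is 0.6 to 1.0 percentage points.

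**The case against.** A reader might infer that concealment fails outright. The documents do not support that. A published block size is not a published sequence. The sequence is computer-generated, handled centrally and concealed with opaque envelopes, and central handling is normally a protection. The researcher is unmasked, but the article does not say that this person enrols students or sees the running tally.

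A reader might also infer that envelopes are filled only when a student is assigned, so that an open list exists until then. That rests on one ungrammatical sentence, which may equally mean that envelopes are used or opened at that moment. No section describes an open list. Who holds the list, and whether envelopes are sealed and numbered, may be set out in the full protocol and cannot be counted as missing here.

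Other features limit the harm:

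- All 700 students are invited by e-mail and there is one exclusion criterion, so there is little discretion over who enters.
- Signed consent and the study guide precede assignment.
- The logistic model includes year of training.
- Both Methods statements agree on permuted blocks, so the intended method is clear.
- A fixed block of 8 is not in itself an error.

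All of this stands, and it limits the size of the point. It does not remove the contradiction in the abstract or the disclosure of what was to be kept from the researcher. The order of enrolment could still be influenced. Adjustment for year does not protect the unadjusted chi-square test and relative risk, and it does not cover unmeasured ability or motivation.

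**Conclusion.** The point holds on two counts. The abstract contradicts the Methods on the allocation method, and the published block size undercuts a safeguard that the protocol says it has. The accurate description is that this safeguard is not secured as written.

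The figures of 20% certain and 66.6% guessed correctly are a worst case. They require an enrolling person who knows the block size and tracks all allocations, which the documents neither state nor rule out. They say how predictable the next assignment could be; no bias in the result has been shown or estimated. The conflict over method matters for balance and correct reporting and has almost no bearing on power or sample size. The point should be corrected before recruitment, but it does not invalidate the design.

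**What to change.** 1. In the abstract, replace simple randomization with permuted blocks.
2. Before recruitment, regenerate the list with randomly varying block sizes. Keep the sizes in a restricted document not available to those who enrol, and say only in public text that block sizes vary and are not disclosed. The secrecy is what helps: if sizes of 4 or 6 were known, 33% or 25% of assignments would be certain, more than with 8. Varying sizes reduce predictability but do not abolish it.
3. Reword the envelope sentence so that each allocation is concealed before assignment and revealed only then.

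The cost is one regeneration of the list and two text corrections. Exact 40:40 balance may be lost by a small margin if the last block is incomplete. The sample size stays at 80.
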